## Abstract

Despite its commercial availability, its high fibre, vitamin C and polyphenol content, there are limited scientific studies exploring the cardiometabolic effects of Baobab fruit powder (BFP) in humans. Due to its high fibre content, BFP may offer a potential intervention to reduce intestinal barrier dysfunction and therefore mitigate cardiometabolic risk. A randomized, double-blind, placebo-controlled trial will be conducted with 50 apparently healthy participants living with obesity. Participants will consume either 16 g of BFP or an isocaloric placebo daily for 45 days. The primary outcome will be intestinal permeability determined using the urinary lactulose/mannitol test. Secondary outcomes include blood biomarkers in intestinal permeability (lipopolysaccharide (LPS), intestinal fatty acid binding protein (IFABP), soluble cluster of differentiation 14 (sCD14) and LPS-binding protein (LBP)), microbiota diversity and composition and cardiometabolic risk markers including glucose levels, blood lipid profiles and blood pressure. Liver and kidney function will be monitored at baseline, after 2 weeks and following 45 days of consumption as safety outcomes. The study protocol ensures rigorous, weekly monitoring of participant compliance and tolerability, along with careful tracking of potential adverse events. Intention-to-treat analysis and mixed effects models will be employed for statistical analyses. Potential selection bias and participant dropout are addressed through thorough recruitment strategies and predefined sample size calculations. This research will contribute to the growing body of knowledge on dietary interventions in the context of cardiometabolic risk, particularly in populations at risk for developing metabolic disease.

South African Clinical Trial Registry - SANCTR, DOH-27-062024-8061; Pan African Clinical Trial Registry – PACTR202308727853680

## Introduction

Baobab (*Adansonia digitata* L.) is an iconic tree indigenous to sub-Saharan Africa. Baobab leaves, seeds, bark, roots and fruit pulp are traditionally used and/or consumed due to their nutritional value and anecdotal health benefits [1,2]. In 2008, Baobab fruit powder (BFP), derived from the fruit of the baobab tree, was authorised as a novel food ingredient in the European Union (EU) and has since been commercially available worldwide. The powder typically contains significant levels of soluble fibre, polyphenols, vitamin C, citric acid and minerals such as calcium, magnesium, potassium and iron [1,3–9]. However, a limited number of studies have explored potential effects of BFP in humans.

To our knowledge few studies have reported potential pre-biotic effects of BFP, showing increased production of short chain fatty acids (SCFA), such as acetate, propionate and butyrate, in faecal cultures from three human donors *in vitro* [9]. Increased intestinal permeability is now a well-established factor implicated in the pathophysiology of metabolic diseases such as obesity and type 2 diabetes, as well as cardiovascular disease [10–14]. The underlying mechanism linking increased intestinal permeability with metabolic diseases is likely the translocation of sub-clinical levels of gut-derived bacterial products such as lipopolysaccharide (LPS) from the intestinal lumen into the blood stream, activating immune responses and resulting in low-grade inflammation characterised by increased levels of C-reactive protein and cytokines such as tumour necrosis factor alpha (TNFα) and interleukin-6 (IL-6) [10,12]. Importantly, interventions such as drugs or herbal formulations with intestinal barrier-protective properties have been shown to improve intestinal permeability [15,16].

Intricately linked with intestinal permeability and homeostasis are commensal microbiota composition and diversity, which are also decreased and/or altered in obesity and type 2 diabetes [17–20]. Diet, and specifically dietary fibre, profoundly affect microbiota composition through selection of saccharolytic bacterial strains that utilise and digest fibres [21,22] and several studies have shown that dietary fibre supplementation can affect microbial composition as well as intestinal barrier function in humans [23–26].

Improved intestinal permeability and microbial composition may modulate dysglycaemia and possibly weight gain. Studies involving healthy adults showed promising acute effects of Baobab fruit extracts on lowering postprandial glycaemia [27,28], while Coe & Ryan [29] reported a reduced 3 hour postprandial insulin response and Garvey *et al.* [30] reported decreased hunger over the 2 hours post consumption.

Based on the reports on the pre-biotic properties in conjunction with the high fibre and polyphenolic content of BFP, we hypothesise that BFP will decrease intestinal permeability, increase intestinal microbial diversity and subsequently lead to improvements in cardiometabolic risk factors. Accordingly, the aim of this study is to perform a randomised double-blind placebo-controlled trial to examine the effects of consumption of BFP on intestinal permeability in participants living with obesity. As secondary aim we will assess the effects of BFP on gut microbiota and cardiometabolic risk factors, as well as confirm the safety for consumption of BFP in humans.

The objectives of this study are to measure the following changes in response to the 45-day BFP intervention compared to the control group:

changes in intestinal permeability using the urinary lactulose/mannitol (Lac/Man) ratio (primary outcome)changes in blood biomarkers of intestinal permeability (secondary outcomes)changes in the composition and diversity of intestinal microbiota profiles using 16S ribosomal RNA gene sequencing (secondary outcomes)changes in cardiometabolic risk markers including anthropometric measurements (such as body mass index (BMI), waist and hip circumference), blood lipid profiles, fasting glycaemia, insulin resistance, inflammation and blood pressure (secondary outcomes)changes in liver (aspartate transaminase (AST), alanine transaminase (ALT), alkaline phosphatase (ALP), gamma glutamyl transpeptidase (GGT)) and kidney (creatinine) function and gastrointestinal symptoms (safety outcomes)

## Methodology

### Study design

In this randomised double-blind, placebo-controlled trial, 50 apparently healthy women and men living with obesity will be randomised at a 1:1 ratio into an experimental (BFP) or a control (placebo) group. Both BFP and the isocaloric placebo will be consumed daily for 45 days.

The schedule of enrolment, intervention and assessments is outlined in Fig 1. Prior to and following the 45-day intervention, participants will complete one testing session, during which the primary and secondary outcomes as well as potential confounders will be measured. To assess safety of BFP, liver (liver enzymes) and kidney (estimated glomerular filtration rate, GFR) function will be assessed at baseline, 2-weeks into the intervention and following the 45-day intervention. Gastrointestinal symptoms will be assessed weekly using validated questionnaires. Participants will be monitored weekly by alternating telephonic contact and visits to the research facility to confirm compliance, acceptability and tolerability. Adverse events, such as allergic reactions, and incidence of other potentially confounding health issues such as illnesses that require extended use of medication will also be assessed. The participants will be encouraged to maintain their usual dietary and lifestyle behaviours during the intervention period. Participants will be reimbursed for their time and travel costs. The overview of the study design is described in Fig 2.

**Fig 1 pone.0328774.g001:**
[figure not shown]
Study schedule of enrolment, interventions and assessment for the proposed randomised placebo-controlled trial.

**Fig 2 pone.0328774.g002:**
[figure not shown]
Study outline for the proposed randomised placebo-controlled trial. Participants meeting the inclusion criteria will be invited to attend the baseline testing session where a urinary intestinal permeability test (lactulose/mannitol test) will be conducted. Socio-demographic, health, physical activity, and dietary data will be entered directly into the electronic data capturing tool (REDCap). Anthropometric (Body mass index, waist and hip circumference) and blood pressure measurements will also be entered into REDCap. Fasting blood samples will be taken to determine safety outcomes (liver and kidney function), as well as blood biomarkers of intestinal permeability and inflammation, fasting glycaemia, insulin resistance and lipid profiles. A stool sample will be requested for analysis of microbiota composition and diversity. The Baobab fruit powder (BFP) group will consume 16 g of BFP and the control group will consume 13.5 g placebo (tapioca flour and citric acid) with similar taste and caloric content daily for 45 days. The testing procedures will be repeated at the 45-day follow-up visit. Participant compliance, tolerability, acceptability and symptoms will be monitored weekly through alternating telephonic contact and visits to the research facility. (Fig 2 was created with BioRender.com).

Ethical approval was obtained from the Human Research Ethics Committees (HREC) at the South African Medical Research Council (reference EC024–11/2022) and University of Cape Town (287/2023). The study will be performed in accordance with the principles of South African Good Clinical Practice (SA GCP 2020 version 3), the Declaration of Helsinki (1964, as amended in Fortaleza Brazil, 2013), the ICH Good Clinical Practice (GCP) and the applicable laws of South Africa. Participants will be required to provide written informed consent prior to participation in the screening and the research study. The trial has been registered with the South African Clinical Trial Registry (SANCTR, DOH-27-062024-8061), the Pan African Clinical Trial Registry (PACTR202308727853680) and received approval from the South African Health Products Regulatory Authority (SAHPRA, Ref 20231121).

#### Participant recruitment and screening.

Participant recruitment and testing sessions will be conducted at the research facility at the University of Cape Town (UCT) in Newlands, Cape Town, South Africa. Awareness will be raised through sharing advertisements via mailing lists and using social media posts on Facebook, LinkedIn and Twitter. Flyers will be distributed at UCT and in the surrounding community to attract participants who are living close to the research facility. Prior to recruitment into the study, participants will undergo screening to confirm their eligibility.

Participants will be invited to attend a screening visit where the purpose of the study and the procedures will be explained in detail and queries regarding the study will be answered. Participants will then sign the informed consent form if they agree to participate in the study and complete a detailed screening questionnaire listing compliance with inclusion (age between 25 and 55 years, body mass index (BMI) ≥ 30 kg/m^2^) and exclusion criteria as detailed in Table 1. Participants with gastrointestinal diseases, previous gastrointestinal surgery, chronic diseases, those taking chronic medication, smokers, pregnant or breastfeeding women will be excluded (Table 1). Body weight, in lightweight clothing without shoes will be measured to the nearest 0.1 kg using a digital scale (Tanita TBF-410GS Total Body Composition Analyzer, Tokyo, Japan), height will be measured to the nearest 0.1 cm using a wall-mounted stadiometer (Holtain, Ltd., Crosswell, UK) [31,32] and BMI will be calculated as weight (kg)/height (m)^2^. After the participant had been seated for at least five minutes, three blood pressure readings will be taken at two-minute intervals using a digital blood pressure monitor (Rossmax, Heerbrugg, Switzerland). After an overnight (10–12 hours) fast, blood samples will be drawn for the measurement of screening parameters including fasting plasma glucose and serum lipid profile (high density lipoprotein (HDL)-cholesterol, low density lipoprotein (LDL)-cholesterol, total cholesterol and triglycerides). Participants that meet all inclusion and exclusion criteria will be enrolled in the study.

**Table 1 pone.0328774.t001:** Inclusion and exclusion criteria.

	*How is it determined:*	*Motivation:*
** *Inclusion criteria* **		
Ability to sign informed consent	Confirmation through questions that participants understand what will be asked of them	Ethical requirement.
Age between 25 and 55 years	Date of birth	This younger age group may be at risk but less likely to display co-morbidities or non-communicable diseases associated with obesity, which could be considered confounders.
Body Mass Index (BMI) ≥ 30 kg/m^2^	Anthropometric measurements	BMI above 30 kg/m^2^ has been associated with increased risk for increased intestinal permeability [33,34].
Weight stable (less than 5 kg weight change in the last 6 months)	Self-reported change in clothes size	Weight change affects cardiometabolic risk factors.
** *Exclusion criteria:* **		
History of gastrointestinal diseases (e.g., irritable bowel syndrome, coeliac disease, Crohn’s disease, Ulcerative Colitis) and gastrointestinal surgery	Self-reported	Effect on intestinal permeability and gut microbiota.
Current smoker (including e-cigarettes) or user of chewing tobacco	Self-reported	Confounding factor for cardiometabolic risk.
Current acute bacterial or viral infection	Self-reported	Potential effect on intestinal permeability and gut microbiota.
Pregnancy or breastfeeding	Self-reported	Ethical considerations
Regular use of chronic (defined as either daily or regular intake at least 3 times per week) medication:		Potential effects on intestinal permeability and gut microbiota.
prescription medication for obesity, chronic non-communicable and infectious diseases	Self reported	
immunosuppressants	Self reported	
frequent use of over-the-counter drugs such as non-steroidal anti-inflammatory drugs and laxatives	Self reported	
Known chronic diseases (with or without treatment with prescription medication) or screen-detected diseases, e.g.,:		Potential effects on intestinal permeability and gut microbiota. Chronic diseases could provide significant confounding factors and may therefore reduce the statistical power of the study.
Autoimmune diseases	Self reported	
Hypertension (BP > 140/90 mm Hg)	Self-reported, blood pressure will be measured on site	
Type 1 or Type 2 diabetes (FBG > 7 mmol/l)	Self-reported, FBG will be assessed	
Dyslipidaemia (TG > 3.0 mmol/l, LDL > 4.0 mmol/l; Participants with TG > 1.7 mmol/l or LDL > 3.0 mmol/l and Framingham risk scores of ≥ 3 for men and ≥ 5 for women [moderate risk and above] [35])	Self-reported, serum lipids will be measured and risk assessed according to Framingham risk scores	
Heart disease	Self reported	
Stroke	Self reported	
Reproductive diseases (e.g., endometriosis or polycystic ovary syndrome)	Self reported	
Thyroid diseases	Self reported	
Infectious diseases (such as HIV)	Self reported	Potential effects on intestinal permeability and gut microbiota
Severe allergies, known allergy to baobab [36] or tapioca flour, and food intolerances (e.g., intolerance to sugar alcohols [mannitol] or lactose intolerance)	Self reported	To avoid risk of sensitisation and new allergic reactions; Food intolerances affect intestinal permeability and can be confounding factors.
Oral antibiotic use, fibre, pre- and/or probiotic supplement use in the preceding 3 months [37,38]	Self reported	Effect on intestinal permeability and gut microbiota.

Abbreviations: BP – blood pressure; FBG – fasting blood glucose; HIV – human immunodeficiency virus; LDL – low density lipoprotein; TG – triglycerides.

Participant recruitment commenced in July 2024. As of June 2025, recruitment, enrolment, data collection and follow up for this trial are ongoing with recruitment expected to be completed by September 2025 and follow up and data collection completed by October 2025.

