#### Intervention and randomisation.

Baobab fruit powder will be supplied by the African Baobab Alliance (ABA), a not-for profit sector organisation representing multiple stakeholders in the Baobab sector, including Baobab fruit harvesters from underserved rural Southern African communities. The BFP provided for this study is a certified organic and natural product and is available in South African supermarkets. It is derived from fruit of the baobab tree that are free-harvested by rural harvesters in the Limpopo Province, South Africa. The BFP surrounds the seeds that are protected by a hard shell. The processing of the fruits includes opening the fruit, separating the seeds from the powder and then milling, sieving and packaging the powder for consumption.

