For the trial, the BFP group will consume 16 g BFP daily for 45 days, while the control group will consume 13.5 g placebo containing tapioca flour and citric acid with a similar appearance and taste to the BFP. The 16 g dose of BFP was selected based on serving suggestions of commercially available products which vary between 8 and 24 g per day. The selected 16 g dose is equivalent to 2 heaped tablespoons and will deliver approximately ~8 g of dietary fibre per day. Previous studies reported long-term use (tolerability) [39], palatability [30], significant changes in postprandial glycaemia [27,28] and insulin response [29] with dosages of 16 g and above. The duration (45 days) was based on studies reporting statistically significant differences in the Lac/Man ratio between the respective intervention and placebo-treated groups [15,40]. To our knowledge, there were no similar studies using a placebo-controlled design to guide the choice of the placebo treatment. The texture and appearance of tapioca flour is similar to BFP, which is important when considering that some participants may be familiar with BFP. Furthermore, tapioca flour does not contain significant levels of dietary fibre (~0.6 g per 100 g), consists predominantly of carbohydrates and contains minimal amounts of other nutrients (https://www.natureschoice.co.za/shop/tapioca-flour-2/). As our study hypothesis is based on the fibre content of BFP (~50%), tapioca flour can be regarded as inert in this context. Therefore, the placebo was chosen to contain tapioca flour (12 g) to mimic the appearance and citric acid (1.5 g) was chosen to mimic the taste of BFP. Citric acid is an organic acid commonly found in fruits and specifically also in Baobab fruit powder [1,6]. The dose for the placebo (13.5 g per day containing ~0.07 g fibre) was calculated to deliver the same energy content as the 16 g BFP (~160 kJ), which is equivalent to half a slice of bread and thus contributes a minor addition to the daily energy intake of our participants. The carbohydrates in tapioca flour are unlikely to have a significant glycaemic impact, however, fasting glycaemia and insulin resistance will be assessed in all participants before and after the intervention. The sachet contents of BFP and placebo can be suspended in up to 1 L of water or added to other cold beverages such as smoothies and juices, or even to cereals. The participants will be encouraged to maintain their usual dietary and lifestyle behaviours during the intervention period. While our study hypothesis is based on the fibre content, BFP, as a food, is also a source of minerals and vitamins [1,6], which may potentially affect gut and cardiometabolic health markers. These vitamins and minerals are integral to the fruit pulp and its properties and should not be considered as confounders. The daily dose of 16 g BFP to be consumed during the intervention would deliver ~20 mg vitamin C, ~ 290 mg Potassium, ~ 30 mg Magnesium and ~50 mg Calcium, based on typical nutritional analysis data [6].

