#### Pre- and post-intervention testing.

On the baseline and follow-up testing days, participants will attend the research facility following a 10–12 hour overnight fast. For 48 hours prior to these testing sessions, participants will be requested to avoid strenuous exercise, alcohol, non-nutritive sweeteners (e.g., in chewing gum and beverages), spicy food, caffeine (including tea), sporadic over-the-counter medication (such as headache pills or other nonsteroidal anti-inflammatory drugs) and supplement use [37,38].

**Stool sampling:** Participants will be given an EasySampler kit to take home for the collection of a pre- and post-intervention stool sample for microbiota analysis. The fresh sample will be aliquoted at the research facility within 6 hours. A pea-sized aliquot of the fresh sample will be removed using a sterile swab and stored in a cryovial prior to microbiota analysis. Approximately 1 g of stool will be weighed for SCFA analysis and all samples will be stored at −80°C.

**Blood sampling:** A fasting venous blood sample (~45 ml) will be collected for the subsequent determination of plasma glucose, serum insulin, serum lipids (triglycerides, total cholesterol, HDL cholesterol and LDL cholesterol), inflammatory markers (e.g., high-sensitivity C-reactive protein [hs-CRP] and biomarkers of intestinal permeability (e.g., LPS, LPS-binding protein [LBP], soluble cluster of differentiation 14 [sCD14], intestinal fatty acid binding protein [IFABP]) as well as safety endpoints (creatinine, aspartate aminotransferase [AST], alanine aminotransferase [ALT], alkaline phosphatase [ALP], gamma glutamyltransferase [GGT]).

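### Table 1 does not clearly exclude recent baobab consumers, and nothing in the protocol bars non-study baobab during the 45 days

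*Protocol article*

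**What the plan says.** Under Participant recruitment and screening, the protocol article checks eligibility against Table 1. Two entries there bear on this point:

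- The allergy criterion, which begins "Severe allergies, known allergy to baobab". This is the only entry that names baobab.
- The supplement criterion: "Oral antibiotic use, fibre, pre- and/or probiotic supplement use in the preceding 3 months". It is self-reported, and the stated reason is an effect on intestinal permeability and gut microbiota.

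Intervention and randomisation says that the test product "is a certified organic and natural product and is available in South African supermarkets". It adds that "BFP, as a food, is also a source of minerals and vitamins" and sets the 16 g dose by reference to "serving suggestions of commercially available products which vary between 8 and 24 g per day". It justifies the look of the placebo by a consideration "which is important when considering that some participants may be familiar with BFP". The Statistical analysis section, by contrast, describes taking the powder as supplementation, and the Introduction refers to its pre-biotic properties.

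For the treatment period, Study design states: "The participants will be encouraged to maintain their usual dietary and lifestyle behaviours during the intervention period". Intervention and randomisation repeats this. The only other restriction on intake is the 48-hour list before each testing session, which ends with "sporadic over-the-counter medication (such as headache pills or other nonsteroidal anti-inflammatory drugs) and supplement use" and does not name baobab. Sachet returns, under Safety and progress monitoring, account for study product only.

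**The concern.** The trial sets out to measure the change over 45 days with the powder against the change without it. That comparison needs a placebo group that is not taking the powder. The protocol excludes users of fibre and prebiotic supplements because these may act on the gut outcomes. It expects the powder to act on the same outcomes through its fibre content of about 50%. The reason for the exclusion therefore applies most directly to the test product, yet the criterion does not name it.

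Commercial servings bracket the trial dose, so a daily consumer could already be near 16 g. If such a person is randomised to placebo and keeps to a normal diet, the placebo group is partly treated. The expected result is a smaller observed difference in the lactulose/mannitol ratio, the microbiota and the cardiometabolic markers. Randomisation balances prior use on average, so the risk is a missed effect and not a false positive.

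**Working it through.** **1. Reading the text**

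| Period | What governs baobab intake | Is baobab named? |
|---|---|---|
| 3 months before entry | Supplement criterion in Table 1, self-reported | No |
| Days 1 to 45 | Encouragement to keep the usual diet | No |
| 48 hours before each test | Pre-test list, including supplement use | No |

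Whether the first row covers the powder depends on whether the participant and the screener regard it as a food or a supplement. The document supports both views. The second row contains no restriction on either view.

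**2. Reproducing the planned sample size**

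Inputs from Sample size determination: means 0.015 and 0.021, SDs 0.006 and 0.007, two-sided alpha 0.05, power 80%, 20 per group.

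- Difference: 0.021 − 0.015 = 0.006.
- Pooled SD: √((0.006² + 0.007²)/2) = 0.00652.
- Standardised difference: 0.006/0.00652 = 0.920.
- Required n per group, t-test: 19.5, so 20. This matches the protocol. (The normal approximation gives 19.)
- Power at 20 per group, t-test: 81.0%.

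**3. Effect of baobab intake in the placebo group**

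Assume that a share f of placebo participants already has the full effect of the powder, and that further intake adds nothing (saturation). The difference becomes 0.006 × (1 − f). With the SD unchanged:

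| f (assumed) | Placebo participants out of 20 | Difference | Power at 20 per group | n per group for 80% |
|---|---|---|---|---|
| 0 | 0 | 0.0060 | 81% | 20 |
| 5% | 1 | 0.0057 | 77% | 22 |
| 10% | 2 | 0.0054 | 72% | 24 |
| 20% | 4 | 0.0048 | 62% | 30 |

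All entries are from the two-sample t-test. Mixing users and non-users also widens the placebo spread slightly. Under the normal approximation, allowing for this lowers power from 79.0% to 78.2% at f = 5% and from 74.5% to 72.9% at f = 10%.

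**4. Partial effect**

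If each user has only a share e of the full effect, f is replaced by f × e. For example, 10% of users with half the effect gives 0.10 × 0.5 = 0.05, which is the 5% row.

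**5. Users in the powder group**

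Suppose the share f is the same in both groups, the effect saturates and the outcome is change from baseline. Users in the powder group then change by 0 and non-users by the full 0.006, so the mean change has size 0.006 × (1 − f). In the placebo group users and non-users both change by 0. The contrast is 0.006 × (1 − f), the same factor as in step 3. If effects instead simply added up with dose, users in both groups would leave the contrast intact.

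**The case against.** The strongest reply is that the supplement criterion already covers the powder. The protocol refers to its pre-biotic properties, puts its fibre content at about 50% and calls its use supplementation. A screener who applied the stated reason for the criterion would have grounds to exclude a regular consumer, and keeping to the usual diet would then mean a diet without baobab. This stands in part: the wording is ambiguous, and a reader who infers that the protocol openly admits habitual consumers goes too far. But a self-reported criterion should not depend on how a participant classes a supermarket food. Even on the favourable reading it ends at entry.

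The screening questionnaire and participant instructions are not shown, and they may ask about baobab. That is possible, but the article prints its eligibility table and twice states the diet instruction, so the gap lies in text that is present.

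Diet is recorded over 3 days at baseline and again at follow-up. This would probably show daily use but could miss irregular use, and it is not linked to eligibility.

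Finally, being familiar with baobab is not the same as eating it regularly, and no figure for use is given. This stands, and the power figures are illustrations only.

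**Conclusion.** The point holds as a gap in the wording of the entry criterion and a missing restriction during treatment. Recent consumers are not clearly excluded, and no rule keeps placebo participants off non-study baobab. The bias would be toward no effect. The size is unknown because the share of users is unknown. On the planning figures, one affected placebo participant in 20 takes power from 81% to about 77%, and two take it to about 72%. This assumes that each has the full effect, that the effect saturates and that the SD is unchanged; with a partial effect the loss is smaller. The design has about one percentage point in hand over 80%, so even one such participant takes it below target.

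Three stronger inferences are tempting but unsupported:

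- That the contrast is removed in both groups. Only affected individuals lose it.
- That users in the powder group dilute the difference further. Step 5 shows the same factor.
- That the advertising attracts baobab eaters. The recruitment text does not say that the advertisements name baobab.

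**What to change.** 1. Extend the 3-month supplement criterion in Table 1 with the words *including baobab fruit powder or baobab-containing products*.
2. Change the diet instruction, in both places where it appears, to *usual diet, without non-study baobab products or fibre, pre- or probiotic supplements*, in force until the day-45 collections are complete.
3. Add a question on non-study baobab and these supplements to the existing weekly contact, and record the answer.
4. Ask participants already enrolled directly about prior and concurrent baobab intake, since the 3-day food record can miss irregular use.
5. Keep the intention-to-treat analysis as primary and report a sensitivity analysis without participants exposed before baseline. Exposure before baseline cannot be influenced by allocation, so this exclusion keeps the groups comparable. Intake after randomisation should be reported by group, not used to drop participants.

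The cost is one eligibility phrase, one instruction, one weekly question and a small protocol amendment, which would probably need review by the two ethics committees and the regulator. A few consumers would be lost to recruitment. Recruitment was expected to end by September 2025, so items 1 to 3 help only the remaining enrolment and participants still under follow-up; items 4 and 5 serve those already enrolled. The planned sample size does not change.
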